#### Cognitive Behaviour Therapy for Insomnia and Depression (CBT-I-D)

Participants who are assigned to the CBT-I-D group will complete the same program as the participants assigned to the CBT-I group (for example, eight sessions of CBT-I); however, the CBT-I-D group will include an additional three CBT strategies to address comorbid depression (behavioural activation, cognitive reframing for depression, and affirmations).

The first additional intervention in this group will include behavioural activation. Behavioural activation, or activity scheduling, is a common intervention included in CBT for depression, which aims to increase an individual’s level of activity, socialisation, and sense of achievement/pleasure [6, 73, 75]. This involves setting behavioural goals and planned activities, and keeping a daily activity schedule to explore how the participants’ feel before and after an activity. These behavioural experiments will be regularly discussed and monitored during the program.

The second and third additional elements of CBT-I-D involve including a broader focus on cognitive reframing and positive affirmations. In addition to reframing sleep-related dysfunctional beliefs, participants in this group will also learn to reframe important negative thoughts related to their depression (for example, [4, 6, 73]). This will be achieved through additional thought records and positive affirmation hope cards introduced during the latter four sessions of the program.

### Control

#### Psycho-Education Control Group (PCG)

Participants assigned to the PCG will also attend eight weekly, 60 to 90 minute sessions, in small groups comprising five to six participants. The content of these sessions will include psychoeducation about sleep, insomnia, and depression, with no active cognitive or behavioural change strategies (for example, instructions, guidelines, homework tasks, relapse prevention). This group will take a more supportive approach rather than a structured CBT format. Morin et al. [41] and Mogenthaler et al. [44] reported that providing only psycho-education is an appropriate control condition in insomnia treatment research.

### Therapists

The therapists who co-facilitate the groups will be provisionally registered psychologists who are completing their final clinical psychology placement within the aged persons’ mental health services. The groups will be co-facilitated due to the heterogeneous and complex nature of this sample. The therapists will receive daily training and clinical supervision throughout the trial by the principal investigator.

### Focus groups

At the end of the final session (Session 8) of each condition, participants will be invited to participate in a focus group to reflect on their experiences from participating in the trial. They will be asked eight questions (for example, ‘What specific strategy was most helpful during the program?’ that have been designed to inform future CBT programs in this field. The focus groups will be conducted by the principal investigator and audio recorded for qualitative statistical analysis. The principal investigator will approach the focus groups in a non-judgemental and curious manner, encouraging open discussion and reflection rather than challenging the participants’ responses [50].

### Randomisation

The randomisation allocation process of participants to treatment groups will comply with CONSORT guidelines (for example, [37]). A block/cluster randomisation design utilising random permuted blocks with randomised block sizes will be implemented to randomly allocate each participant group to one of three conditions throughout the trial. Block randomisation is commonly used in small- to moderate-sized RCTs to ensure that approximately equal numbers of participant groups in the clustered context are allocated to each condition [67]. The computer-generated random allocations will be generated by an independent researcher at Federation University Australia and will be stored on a password-protected computer back-up to a secure university file server. Random allocation will occur after the pre-treatment assessments have been completed to ensure eligibility has been met. Each successive random allocation will be communicated to the principal investigator only when five to six eligible participants are ready to commence a group. Participants will be unaware of the study’s hypotheses or which group they have been randomly allocated. The co-therapists will not be blinded to the treatment conditions.

### Sample size calculation

Statistical power analysis was based on an examination of treatment-time interactions in a repeated measures analysis of covariance (RMANCOVA) of the ISI measure [38], with adjustment for confounders. We specified an initial value of 18 points in the adjusted mean of the ISI score at pre-intervention [22]; a mean reduction of 10 points from pre- to post-intervention for the CBT-I treatment [22]; and a target value of two points difference between the pre-post changes for each of the three treatment conditions (that is, -8, −10, and −12 points, respectively) [43], with no further change at follow-up [43], and assuming a ‘within-treatments’ SD of 3.4 points [22]. This resulted in an effect size of 0.23. Under the assumptions of constant correlation over time (sphericity), with an estimated magnitude of *r* = 0.6 based on reported test-retest reliabilities of 0.79 [14] and 0.86 [76], and allowance for a design effect [16] of 1.07 due to clustering of participants within treatment groups (based on an assumed cluster size of five and an intra-class correlation of 0.017, [22]), with a significance level of 5 % and 80 % power, the required sample size calculated using GPower software [20] is *N* = 35 (33 × 1.07). Maintaining the same specifications, but focusing solely on the CBT-I and CBT-I-D conditions, the specific target difference of two points between the pre-post changes for these two particular treatments corresponds to an effect size of 0.13. In order to have 80 % power to detect this particular difference in a post hoc pairwise comparison, the required sample size is increased to *N* = 85 (78 × 1.07).

With regard to the GDS measure [74], Secker and Brown [57] reported pre- and post-intervention means of 7.0 and 4.4 in a treatment group, and 5.8 and 4.7 in a control group, a difference of 1.5 units [(7.0 - 4.4 = 2.6) - (5.8 - 4.7 = 1.1)] in the pre- and post-change, and an average within-treatment *SD* of 3.5. Replacing the values of 2.0 and 3.4 in the ISI analysis with 1.5 and 3.5 results in effect sizes of 0.16 with respect to comparisons across the three conditions and 0.10 with respect to comparisons between the two conditions. This leads to required sample sizes of *N* = 68 with respect to comparison of mean GDS across the three conditions, and *N* = 150 with respect to comparison of mean GDS between two of the conditions. Because this is larger than *N* = 85 from the ISI projection, *N* = 150 becomes our target sample size, which equates to 50 participants or 10 groups per condition.

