## Methods/Design

### Trial design

This trial will follow the International CONSORT (Consolidated Standards of Reporting Trials) guidelines and evaluate conditions using a randomised control trial (RCT) design [56]. Participants who are eligible for the trial will be randomly allocated to one of three conditions: CBT-I, CBT-I-D, or PCG. Outcomes will be assessed at pre-intervention (week 0), post-intervention (week 8), and 3-month follow-up (week 20). Figure 1 illustrates the study’s design and expected participant flow chart.

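### The pairwise sample sizes do not follow from their stated inputs: 74 rather than 85 for the ISI, and 137 to 139 rather than the 150 adopted as target for the GDS

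*Protocol article*

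**What the plan says.** All of this stands under Sample size calculation in the protocol article. The calculation concerns the treatment-by-time interaction in a repeated measures analysis, run in GPower. The ISI inputs are "a target value of two points difference between the pre-post changes for each of the three treatment conditions" (changes of -8, -10 and -12), "with no further change at follow-up", a within-treatment "SD of 3.4 points", a constant correlation of 0.6 over time, a 5% significance level, 80% power and a design effect of 1.07. Under Trial design, outcomes are measured at weeks 0, 8 and 20.

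For three conditions the article reports an effect size of 0.23 and N = 35 (33 × 1.07). For CBT-I against CBT-I-D alone, on the same specifications, the two-point difference "corresponds to an effect size of 0.13", and "the required sample size is increased to" 85, shown as 78 × 1.07.

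For the GDS, putting 1.5 and 3.5 in place of 2.0 and 3.4 "results in effect sizes of 0.16 with respect to comparisons across the three conditions and 0.10 with respect to comparisons between the two conditions". The required totals are given as 68 and 150. Because 150 exceeds 85, it becomes the target, described as 50 participants or 10 groups per condition.

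**The concern.** The target of 150 rests on the GDS pairwise figure alone, and the comparison of CBT-I-D with CBT-I is the one the article singles out under Aims and hypotheses. If the figure cannot be obtained from its printed inputs, a reader cannot check the trial's main power statement or tell whether 150 contains an undeclared allowance. The ISI pairwise effect size also looks too small for a two-point difference with an SD of 3.4.

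**Working it through.** **Method.** For a within-between interaction with k conditions, m = 3 time points and correlation ρ = 0.6:

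- f = (root mean square of the interaction cell effects) / SD
- λ = f² × N × m / (1 − ρ) = 7.5 × f² × N
- df1 = (k − 1)(m − 1) and df2 = (N − k)(m − 1)
- N is the smallest total for which the noncentral F test at 5% has at least 80% power. It is then multiplied by 1.07.

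**Reproducing the article's three-condition figures.**

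- ISI: f = 0.226, printed as 0.23. With 0.23, N = 33, and 33 × 1.07 = 35.3. The article prints 33 and 35.
- GDS: f = 0.165, printed as 0.16. With unrounded f and equal groups, N = 63, and 63 × 1.07 = 67.4. The article prints 68.

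The method is therefore very likely the article's own.

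**ISI, two conditions.**

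1. The cell means are (18, 8, 8) and (18, 6, 6).
2. The interaction effects are ±0.667 at week 0 and ±0.333 at each of weeks 8 and 20.
3. Sum of squares: 2 × (0.444 + 0.111 + 0.111) = 1.333. Divided by six cells this is 0.2222, with square root 0.4714.
4. f = 0.4714 / 3.4 = 0.1386, which rounds to 0.14. The article prints 0.13.
5. With f = 0.1386, N = 69 (70 with equal groups), and 69 × 1.07 = 73.8, so 74.
6. With the printed f = 0.13, N = 78. The article's 78 is thus a consequence of its effect size and not a second error.

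**GDS, two conditions.**

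1. The root mean square scales with the difference: 0.4714 × 1.5 / 2 = 0.3536.
2. f = 0.3536 / 3.5 = 0.1010. The printed 0.10 is correct.
3. With f = 0.1010, N = 128, and 128 × 1.07 = 137.0.
4. With f rounded to 0.10, N = 130, and 130 × 1.07 = 139.1.
5. The article prints 150. To reach it (140 × 1.07 = 149.8), f would have to be about 0.097.

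| Pairwise case | f printed | f recomputed | N printed (after design effect) | N recomputed (after design effect) |
|---|---|---|---|---|
| ISI | 0.13 | 0.139 | 78 (85) | 69 (74) |
| GDS | 0.10 | 0.101 | not given (150) | 128 to 130 (137 to 139) |

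**Alternatives tried.**

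- Two time points only: the GDS needs 139, or 148.7 after the design effect, which is close to 150. The effect sizes would then be 0.107 (GDS) and 0.147 (ISI), and the ISI total would be 75, or 80 after the design effect. These contradict the printed 0.10, 0.13 and 85.
- Multivariate degrees of freedom: 80 (85.6) at f = 0.13, but only 132 (141) at f = 0.10.
- Change-score and ANCOVA formulas, and other values of ρ and the significance level: none reproduces all the pairwise figures.

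**What 50 per condition delivers.** A pairwise comparison has 100 participants, or 100 / 1.07 ≈ 93 effective. Power is about 91% for the ISI (f = 0.1386) and 65 to 66% for the GDS (f = 0.10 to 0.101).

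**The case against.** The best defence is recruitment in whole groups. Participants are allocated in groups of five to six, the assumed cluster size is five, and the target is expressed in groups. Nine groups of five in each of three conditions make 135, which falls short of 137 to 139. Ten make 150. Likewise 78 × 1.07 = 83.5 becomes 85 when raised to the next multiple of five. This is plausible, and for that reason the gap between 83.5 and 85 should not be counted as an error of its own. But the article states no such rule and calls 150 the required size. The rule also does not fit the printed 68, and 85 is 17 groups, which cannot be divided equally between two or three conditions.

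A second defence is that the discrepancies do no harm, and taken alone that stands. If 150 were placed in two conditions (about 140 effective), GDS power would be 83 to 84%. If 85 were (about 79 effective), ISI power would be about 86%.

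Three stronger readings are tempting and are not supported:

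- **Both pairwise effect sizes are wrong.** Only the ISI value is. The GDS value of 0.10 follows from its inputs.
- **The arithmetic slip leaves the trial short of power.** It errs the other way. The 65 to 66% for the GDS arises because a two-condition total is spread over three conditions. It would be the same had the article printed 0.139, 74 and 137.
- **The origin of 0.13 is known.** Keeping a third condition, equal to one of the pair, in the effect size gives 0.131 for the ISI. The same step gives 0.095 and a total of about 154 for the GDS, which matches neither 0.10 nor 150. It remains conjecture.

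**Conclusion.** The point holds as a failure of the printed figures to follow from their inputs. The ISI pairwise effect size is 0.139 and not 0.13, which makes the printed total about 15% too high (85 against 74). The GDS effect size is right, but the total is 8 to 9% too high (150 against 137 to 139) with no stated step between. It merits correction because 150 is the trial's target and has no other justification. It does not show that 150 is too small or that more participants must be enrolled.

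The result assumes the GPower within-between interaction test, three time points, sphericity with a correlation of 0.6, equal means at weeks 8 and 20, and the article's design effect. The three-condition figures support that reading of the method.

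**What to change.** Under Sample size calculation:

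1. Restate the pairwise figures as ISI f = 0.139, N = 74 and GDS f = 0.101, N = 137. If 150 was reached by rounding up to equal numbers of whole groups in three conditions, state that rule.
2. Label the pairwise figures as totals over two conditions.
3. Report the power that the fixed 50 per condition gives for a pairwise comparison after the design effect: about 91% for the ISI and 65 to 66% for the GDS. The GDS shortfall should be attributed to dividing a two-condition total among three conditions, which is a separate matter.

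The cost is a few sentences of text. Correcting these figures does not itself change enrolment, allocation or trial conduct.

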**Methods/Design:**

We aim to recruit 150 older adults with comorbid insomnia who have presented to community mental health services for depression. Eligible participants will be randomly allocated via block/cluster randomisation to one of three group therapy conditions: CBT-I, CBT-I-D, or PCG. Participants who receive CBT-I will only practice strategies designed to improve their sleep, whereas participants who receive CBT-I-D will practice additional strategies designed to also improve their mood. This trial will implement a mixed-methods design involving quantitative outcome measures and qualitative focus groups. The primary outcome measures are insomnia and depression severity, and secondary outcomes are anxiety, hopelessness, beliefs about sleep, comorbid sleep conditions, and health. Outcomes will be assessed at pre-intervention (week 0), post-intervention (week 8), and 3-month follow-up (week 20).

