### Statistical analyses

Data will be entered, screened, and analysed using SPSS Version 21 [25]. A RMANCOVA will be implemented to explore differences between the conditions over time, and calculate effect sizes to investigate the treatment effect. An intention-to-treat methodology will be applied via multiple imputation. The qualitative data obtained from the focus groups will be analysed according to the Interpretative Phenomenological Analysis (IPA) method (for example, [50, 63]). This will be achieved by transcribing the data verbatim from audio recordings into text. The text transcripts will be read several times to extract emerging codes, which will then be transformed into themes [50]. Themes are likely to identify both something of importance to the participants, and also convey a meaning of their reflection [63]. These themes will form the basis for the qualitative results. Direct quotes from the participants will also be reported to highlight the thematic findings [63].

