Finally, we are interested in studying the participants’ experiences from taking part in a CBT trial for insomnia and depression. The information gained from a mixed methods design will provide an opportunity to gather rich, personal data through older adults that can either confirm or disconfirm the questionnaire outcome measures [13, 33]. This can open new avenues of explanation for particular findings that traditional quantitative measures cannot detect [47]. For example, results from the reflective focus groups may indicate participants benefitted from specific CBT strategies that would not be revealed through quantitative data [33]. In addition, participants may provide innovative feedback that is particularly relevant to the delivery of CBT-I among this complex aged population. Therefore, it is expected that the qualitative findings from this project will enhance the direction of future research in this field.

Despite the important implications that may result from this study protocol, the project will likely include limitations. First, no physiological measure of sleep (for example, polysomnography) will be assessed to cross-validate the clinical interview and self-report data. This means that the assessments throughout the trial will be reliant on subjective measures from the participants and researchers, as opposed to objective biological data. Since no standardised clinical diagnostic instrument has been established yet for the *DSM-V*, the authors updated existing *DSM-IV* diagnostic instruments (for example, MINI 6.0) to be consistent with the *DSM-V* diagnostic criteria. Finally, participant recruitment and retention rates could be negatively affected due to this population likely experiencing stronger symptoms of tiredness, hopelessness, and amotivation. Hence, recruiting participants and keeping them engaged throughout the program will likely create significant challenges. Notwithstanding these limitations, the results following this study protocol will likely contribute important knowledge that improves case formulation and treatment planning for older adults with comorbid insomnia and depression.

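### The GDS sample size of 150 is also the recruitment target, with no allowance for loss; with 50 per condition the CBT-I-D versus CBT-I comparison has about 65% power before any loss and about 54–63% at an assumed 20% loss

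*Protocol article*

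**What the plan says.** The protocol article's Sample size calculation section sets out its inputs for the ISI: the treatment-by-time interaction in a repeated measures analysis, a constant correlation over time of 0.6, "with a significance level of 5 % and 80 % power", and "allowance for a design effect [16] of 1.07 due to clustering of participants within treatment groups". That factor comes from groups of five and an intra-class correlation of 0.017.

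The GDS calculation reuses this set-up with "a difference of 1.5 units" in pre-post change and an SD of 3.5. The resulting effect size is 0.10 for two conditions, and the required size is 150. This is the largest requirement in the section, so it "becomes our target sample size, which equates to 50 participants or 10 groups per condition".

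The abstract (Methods/Design) gives the same figure as the number to enrol: "We aim to recruit 150 older adults with comorbid insomnia". Outcomes run to week 20.

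The limitations part of the Discussion says that "participant recruitment and retention rates could be negatively affected due to this population likely experiencing stronger symptoms of tiredness, hopelessness, and amotivation", and expects that keeping people engaged will be a significant challenge. It gives no rate. On missing data, Statistical analyses says: "An intention-to-treat methodology will be applied via multiple imputation".

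**The concern.** A number required for analysis and a number to be recruited are the same only if everyone recruited supplies the outcome. Here they are the same, and the one inflation factor is for clustering. The protocol names retention as a likely difficulty but does not carry it into the calculation.

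Multiple imputation keeps all randomised participants in the analysis. It cannot recreate the information in week 8 and week 20 scores that were never observed.

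The comparison affected is the one that set the sample size, and CBT-I-D against CBT-I is the stated particular focus of the aims. The Discussion says the results could show that CBT-I is sufficient for both conditions. If power is well below 80%, a non-significant GDS difference is weak support for that conclusion, and a reader relying on the stated 80% would give it too much weight.

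**Working it through.** **Inputs (Sample size calculation).** Significance level 5%, power 80%, r = 0.6 with sphericity, m = 3 time points (weeks 0, 8, 20), f = 0.10 for GDS with k = 2 conditions, design effect 1 + (5 − 1) × 0.017 = 1.068, stated as 1.07. Allocation is 50 per condition, so two conditions hold 100. Loss rates of 10%, 20% and 30% are assumptions.

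**Formula.** Within-between interaction F-test: λ = f² × N × m / (1 − r), df1 = (k − 1)(m − 1), df2 = (N − k)(m − 1). N is the number of people divided by 1.07.

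**Reproducing the plan.**
- ISI, three conditions, f = 0.23: N = 33 (stated 33).
- ISI, two conditions, f = 0.13: N = 78 (stated 78).
- GDS, three conditions, f = 0.16: 65 × 1.07 = 69.6 (stated 68, close).
- GDS, two conditions, f = 0.10: 130 × 1.07 = 139 (stated 150). The 150 is recovered with f near 0.096, which also rounds to 0.10 (140 × 1.07 = 150). It is also recovered by a t-test on pre-post change with SD 3.5 × √0.8 = 3.13 (70 per arm, 140 × 1.07 = 150).

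In each version that gives 150, it is the total for two conditions, or 75 per condition.

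**Power when lost participants contribute nothing.** Worked case, 100 in the pair and no loss: N = 100 / 1.07 = 93.5; λ = 0.01 × 93.5 × 3 / 0.4 = 7.01; power 65%. At 20% loss: N = 80 / 1.07 = 74.8; λ = 5.61; power 54%.

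| Assumed loss | 100 in the pair (50 per condition) | 150 in the pair (the plan's count) |
|---|---|---|
| 0% | 65% | 83% |
| 10% | 60% | 79% |
| 20% | 54% | 73% |
| 30% | 49% | 67% |

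On the plan's count with f = 0.10, power stays at 80% up to about 7% loss, because 139 are needed and 150 are counted (1 − 139/150 = 0.07). With f = 0.0964 there is no such slack: 80% with no loss and 70% at 20% loss. For 100 in the pair, the same f gives 61% and 51%.

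**Power when observed visits are used.** The plan assumes the full effect at week 8 and no further change at week 20. With r = 0.6 between all visits and loss at random, I calculated the share of information on that effect that remains when 20% of participants have incomplete data, and multiplied λ by it:

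| Who is lost (20% in total) | Information kept | 100 in the pair | 150 in the pair |
|---|---|---|---|
| All miss week 20 only | 95% | 63% | 81% |
| Half miss week 20 only, half miss both | 90% | 60% | 79% |
| All miss both | 85% | 57% | 76% |

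**The case against.** Five objections deserve an answer.

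**Loss modelled too harshly.** Deleting every lost participant is close to the worst case. Everyone has a baseline score, some will have week 8, and imputation uses both. This stands: at 20% loss the figure for 100 in the pair is 57–63%, not only 54%, provided loss is at random and the imputation model is well specified. None of these figures reaches 80%.

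**There is slack.** On the plan's count and the printed f = 0.10, about 7% loss is tolerable. A reader might therefore infer either that the plan has a margin or, conversely, that it requires complete follow-up. Neither is quite supported. The slack comes from f being printed to two decimals, is not described as an allowance, vanishes if f is near 0.096, and does not exist with 100 in the pair.

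**The protocol only cautions.** It does not forecast a rate of loss, and it would be wrong to say that it predicts 20%. This stands, which is why the rates above are a range and are labelled as assumed.

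**Groups may be larger than five.** The Interventions, Control and Randomisation sections give groups of five to six, so 30 groups could hold 150–180 people. The article does not call this a margin, and its recruitment figure remains 150.

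**Allocation matters more.** Counting 100 instead of 150 takes power from 83% to 65% with no loss, more than 20% loss does on either count. That is true, but loss comes on top of it.

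**Conclusion.** The point holds. The size required for 80% power on the two-condition GDS comparison is also the number to be recruited, no allowance for loss is made, and the protocol itself warns about retention. For the design as described, with 50 per condition, power for CBT-I-D versus CBT-I on the GDS is about 65% before any loss. It falls to about 60%, 54% and 49% at assumed losses of 10%, 20% and 30% if lost participants contribute nothing, and is about 57–63% at 20% loss if their observed visits are used.

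A reader might infer that the effect of 20% loss is simply a fall from 80% to 73%. The documents do not support that as the headline, because 73% places all 150 participants in a comparison of two conditions while the protocol places 100 there. Nor is 150 shown to be an arithmetic error as a two-condition total, since an unrounded f or a t-test on change recovers it.

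The figures rest on the plan's effect size, correlation and design effect, and on loss rates that the protocol does not give. Letting the design effect shrink as groups lose members changes the 20% figure by only about one point (55% instead of 54%).

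**What to change.** Keep 150 as the recruitment target. In the GDS paragraph of Sample size calculation:

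1. State an assumed range for the share of participants with week 8 and week 20 outcomes, labelled as an assumption.
2. Restate the power of the pairwise GDS comparison for 50 per condition over that range. For example: about 65% with complete data; about 54–60% at 80–90% retention if those lost contribute nothing; about 57–63% at 80% retention if observed visits are used through imputation.
3. Remove the implication that recruiting 150 delivers 80% power for this comparison.

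This takes one or two sentences and changes neither the number recruited, the design nor the analysis. The downside is a less favourable stated power for the comparison that set the size.
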